## **Appendix 4:**

### **Study protocol**

#### **Study medication**

- Group A: ezetimibe 10 mg/day
- Group B: simvastatin 40 mg/day
- Group C: ezetimibe 10 mg/day plus simvastatin 40 mg/day

Study medication will be obtained free of charge through the hospital pharmacy of the University of Cologne (“Handelsware Ezetrol® 10 mg, Zocor® forte”).

There will be open label treatment.

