##### **Randomization**

Eligibility for study participation will be determined by use of a standardized medical history questionnaire. Informed consent will be obtained, a physical examination and screening routine laboratory chemistry will be performed. All enrolled patients will be randomized to receive either ezetimibe, simvastatin or both.

Randomization will be performed according to a predetermined random list (balanced 6-block design) by use of sealed envelopes.

Before randomization, all selection criteria must be checked by filling in the inclusion/exclusion criteria form in the CRF.

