### *Visit 1 (qualifying visit)*

- Medical history (visit to doctor's office, evaluation of standardized questionnaire)
- Informed consent
- Baseline screening (inclusion/exclusion criteria)
- Physical examination
- Baseline safety laboratory
- Fasting blood sample (study parameters V1)
- Randomization

*Note:* Explanation of the terms and conditions of the study to the volunteers will be executed in a seminar-like group appointment preceding Visit 1.

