### *Visit 2 (within 7 days after Visit 1)*

- Fasting blood sample (study parameters V2)
- Dispense of medication

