#### *Inclusion criteria*

- Male volunteers who are mentally and linguistically able to understand the aim of the study and to show sufficient compliance in following the study protocol
- Age between 18 and 60 years
- Patients must be generally in good or adequate health according to the judgement of the investigator and based on the history, physical examination and laboratory screening
- Body mass index between 18,5 and 30 kg/m^2
- LDL cholesterol < 190 mg/dl, triglycerides < 250 mg/dl
- Normal blood pressure (< 140/90 mmHg). Isolated systolic blood pressure (RR syst. > 140 mmHg, diast. < 90 mmHg) is acceptable if subject is otherwise in good health.
- Written informed consent before enrolment in the study

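### Randomisation is scheduled at Visit 1, alongside the first laboratory draw and up to 7 days before the only mechanistic baseline, so the schedule secures neither the eligibility check nor a pre-allocation baseline

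*Protocol*

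**What the plan says.** **Eligibility rule.** Appendix 4, Randomization, states: "Before randomization, all selection criteria must be checked by filling in the inclusion/exclusion criteria form in the CRF". The same section opens with "Eligibility for study participation will be determined by use of a standardized medical history questionnaire" and only then mentions the physical examination and screening chemistry.

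**Schedule.** The visit headed "Visit 1 (qualifying visit)" lists, among other items, "Baseline safety laboratory", a fasting sample and, as its last item, "Randomization". Visit 2 follows within 7 days. It lists "Fasting blood sample (study parameters V2)" and then the dispensing of medication.

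**Criteria that need blood results.** Appendix 5 requires "LDL cholesterol < 190 mg/dl, triglycerides < 250 mg/dl". It also excludes men on a transaminase limit (above 2 x ULN) and on a Cockcroft-Gault GFR below 60 ml/min, which needs creatinine.

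**Blinding and replacement.** Appendix 4, Study medication, says "There will be open label treatment". Allocation is by sealed envelope in blocks of 6. Drop-outs are replaced until each group has 20 completers.

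**The concern.** Two separate things are at stake.

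1. **Eligibility before allocation.** If the laboratory values are not back when the envelope is opened, the investigator has two options for a man who then fails: remove him after randomisation with his arm known, or keep him although he does not meet the criteria. The first breaks the block balance and lets exclusion depend on arm. The second departs from the protocol's own rule.

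2. **Baseline before allocation.** In an open-label trial, a baseline measured after allocation is not protected by randomisation in the usual way. A man who knows his arm can change his behaviour or withdraw before the sample is drawn. Because drop-outs are replaced, such a withdrawal would not show among the 60 completers. The primary objective concerns HMG-CoA reductase activity and expression and LDL receptor expression and protein. Appendix 3 itself describes cholesterol synthesis as responding to plant-sterol foods and, in rats, HMG-CoA reductase as responding to cholesterol feeding.

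**Working it through.** **Step 1: is there blood before Visit 1?** No. The pre-study contact is by telephone, with criteria documented only as far as that allows. Section B.3 counts three blood draws, two at baseline and one at the end, and these match Visits 1, 2 and 3. The Visit 1 draw is therefore the first source of study laboratory values.

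**Step 2: which criteria depend on that draw?** Four have explicit laboratory limits: LDL, triglycerides, transaminases and creatinine-based GFR. General health is also judged partly on laboratory screening. Diabetes and other endocrine disorders are excluded without a laboratory threshold, so history could settle those.

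**Step 3: where is each outcome first measured?**

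| Outcome | Visit 1 | Visit 2 | Visit 3 |
|---|---|---|---|
| LDL receptor and HMG-CoA reductase mRNA | no | yes | yes |
| LDL receptor surface protein | no | yes | yes |
| Serum lathosterol | no | yes | yes |
| Lipoproteins | yes | yes | yes |

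The sources are the tube list under Sample collection and handling of samples, the list headed Study parameters (Visit 2 and 3), and Safety laboratory parameters. The Visit 1 tubes cover safety chemistry with lipoproteins, blood count, glucose and thyroid. There are no RNA tubes and no tubes for other study parameters. The Visit 1 schedule nevertheless labels its fasting sample as a study-parameter sample for that visit, which the other two lists do not provide for. These places need to be reconciled.

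**Step 4: the order of events as scheduled.** Randomisation at Visit 1; then 0 to 7 days; then the Visit 2 sample; then dispensing. For the first three rows of the table, baseline follows allocation in all 60 men. It precedes the first dose in all of them.

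**Step 5: the stated size.** 3 groups x 20 = 60 completers, and 60 / 6 = 10 full blocks. This reproduces.

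**Step 6: illustration of the eligibility part.** The protocol gives no rate of laboratory failure, so p is an assumption. The figures apply only if envelopes are opened before results are read.

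- Envelopes used on ineligible men among the first 60: 60p.
- Chance that a block of 6 loses at least one man: 1 - (1 - p)^6.
- Men to randomise to reach 60 eligible men: 60 / (1 - p), rounded up.
- Chance of at least one ineligible man among 60: 1 - (1 - p)^60.

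| Assumed p | 60p | Block loses at least one | Randomised for 60 eligible | At least one among 60 |
|---|---|---|---|---|
| 0 (results read first) | 0 | 0% | 60 | 0% |
| 5% | 3 | 1 - 0.735 = 26% | 64 | 95% |
| 10% | 6 | 1 - 0.531 = 47% | 67 | 99.8% |
| 15% | 9 | 1 - 0.377 = 62% | 71 | >99.9% |

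The documents give no figure from which to size any bias from the post-allocation baseline, so none is offered.

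**The case against.** The strongest reply is that the protocol already forbids what is feared. All criteria must be checked first, randomisation is the last Visit 1 item, and blood is drawn between 7:00 and 9:00, so same-day results are possible. The telephone contact and questionnaire also remove some unsuitable men beforehand. This stands. A reader might infer from the schedule that men are randomised before the laboratory results exist, and so that ineligible men do receive allocations. The protocol does not say that. It gives no turnaround time in either direction, so the eligibility part is conditional: the schedule does not secure the rule, but does not necessarily break it.

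On baseline, the reply is that the Visit 2 sample is untreated in every arm and meets the Summary's definition of baseline as before treatment starts. The outcomes are laboratory assays, 7 days is a maximum, and nothing says when volunteers learn their arm. These points limit how likely a bias is. They do not restore a pre-allocation baseline: no text conceals the arm between the visits, and the sampling instructions restrict only overnight fasting, alcohol the day before and smoking that morning. A reader might also infer that no outcome has a pre-allocation value, which is too broad, because lipoproteins are measured at Visit 1.

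Finally, the 5% to 15% failure rates come from no document, and the range must include zero. That is accepted, and the table shows zero.

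**Conclusion.** The point holds in two parts.

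- **Eligibility (conditional).** Scheduling randomisation at the visit of the first laboratory draw keeps the protocol's rule only if every result is back and recorded before the envelope is opened. The protocol does not state this. The number of men affected is zero if that happens. If it does not, the number depends on an unstated failure rate; the 3, 6 or 9 of 60 above are illustrations.
- **Baseline (not dependent on turnaround).** For mRNA, receptor protein and lathosterol, the only pre-treatment sample is scheduled up to 7 days after an open-label allocation. Arm-dependent behaviour or withdrawal before baseline is possible, and replacement of drop-outs would hide the withdrawals. Whether this happens, and how much it would shift a change from baseline, is unknown.

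Severity is moderate. The documents do not show that ineligible men are randomised or that the results are biased. They do show a sequence that leaves both open without need, and that cannot be repaired once men have been enrolled.

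**What to change.** Delete randomisation from the Visit 1 list and specify this order at Visit 2:

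1. Visit 1 laboratory results reviewed and the criteria form completed.
2. Visit 2 fasting sample drawn.
3. Envelope opened.
4. Medication dispensed.

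Men who fail a laboratory criterion then become screen failures and use no envelope, and every mechanistic baseline precedes allocation. Visit 2 already exists and is where medication is dispensed, so the change needs no extra visit, sample or subject. The 60 completers and ten blocks of 6 are unchanged.

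Two text corrections belong with it. Reword the opening sentence of the Randomization section so that the questionnaire does not appear to settle eligibility alone. Reconcile the study-parameter label on the Visit 1 sample with the tube list and the study-parameter list.

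A lesser alternative is one sentence saying that the envelope is opened only after the Visit 1 results are recorded. If randomisation stayed at Visit 1, that would close the eligibility part but leave the baseline after allocation.

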##### **Study Schedule**

###### *Pre-study telephone visit*

- Determine and document inclusion and exclusion criteria as far as possible
- Send questionnaire

### *Visit 1 (qualifying visit)*

- Medical history (visit to doctor's office, evaluation of standardized questionnaire)
- Informed consent
- Baseline screening (inclusion/exclusion criteria)
- Physical examination
- Baseline safety laboratory
- Fasting blood sample (study parameters V1)
- Randomization

*Note:* Explanation of the terms and conditions of the study to the volunteers will be executed in a seminar-like group appointment preceding Visit 1.

### *Visit 2 (within 7 days after Visit 1)*

- Fasting blood sample (study parameters V2)
- Dispense of medication

### *Visit 3 (14 days after Visit 2)*

- Fasting blood sample (study parameters V3)
- End of study safety laboratory
- End of study examination
- Collection of study medication, pill count (compliance)

## **Study medication, dosage and duration of treatment**

Medication and dosage:

- Group A: ezetimibe 10 mg/day (Ezetrol® 10 mg Tabletten), 1 tablet per day
- Group B: simvastatin 40 mg/day (Zocor® forte 40 mg) , 1 tablet per day
- Group C: ezetimibe 10 mg/day plus simvastatin 40 mg/day (Ezetrol® 10 mg Tabletten and Zocor® forte 40 mg) , 1 tablet *each* per day

The subjects will be asked to take the study medication once daily *in the evening*. There is no need to take the medication in specific relation to food consumption. The last dose should be taken approximately 12 hours before blood sampling.

## **Description of the method**

### **Sample collection and handling of samples**

- Fasting blood sample drawn between 7:00 and 9:00 h after a >10-h overnight fast.
- Subjects will abstain from drinking alcohol the day before and from smoking on the morning of blood sampling.
- Samples to be drawn:
  - Visit 1:
    - 1 serum monovette for routine safety lab including lipoproteins
    - 1 EDTA monovette for blood count
    - 1 NaF monovette for plasma glucose
    - 1 serum monovette for thyroid parameters

- Visit 2:
  - 1 serum monovette for lipoproteins
  - Three 10 ml EDTA tubes for RNA analysis
  - Three 10 ml serum monovettes for other study parameters
- Visit 3:
  - 1 serum monovette for routine safety lab including lipoproteins
  - 1 EDTA monovette for blood count
  - Three 10 ml EDTA tubes for RNA analysis
  - Three 10 ml serum monovettes for other study parameters

Handling of samples is described on separate sheet.

### **Study parameters (Visit 2 and 3)**

- LDL receptor and HMG-CoA reductase mRNA as well as LDL receptor cell-surface protein expression will be analyzed in mononuclear blood cells.
- Serum lathosterol
- Serum lipoproteins (total cholesterol, LDL, HDL, triglycerides) → see safety parameters

### **Safety laboratory parameters**

#### *Visit 1*

Na, K, Ca

Creatinine

GOT, GPT,  $\gamma$ -GT

CK

Serum lipoproteins (total cholesterol, LDL, HDL, triglycerides)

CRP

Glucose

Whole blood cell count

TSH, fT4

#### *Visit 2*

Serum lipoproteins (total cholesterol, LDL, HDL, triglycerides)

Whole blood cell count

#### *Visit 3*

GOT, GPT,  $\gamma$ -GT

CK

Serum lipoproteins (total cholesterol, LDL, HDL, triglycerides)

CRP

Whole blood cell count

### **Number of centers and number of subjects**

*Number of investigational sites:* This is a one-center trial.

*Number of subjects:* A total number of subjects of 20 in each treatment group is required (20 completed cases per group, drop-outs will be replaced). Total number: 60 completed subjects.

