## **10. Multicenter trials**

This trial is a monocenter study.  
Approximately 60 subjects will be recruited at the University of Cologne.

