## **10. Interim analysis and criteria for early termination**

There will be no interim analysis. The planned number of participants and the analyses will have to be reached before the study will be evaluated.

The termination criteria for the individual participant will be according to general clinical practice using ezetimibe or simvastatin.

Early termination of the whole trial will not be expected, therefore no specific criteria will be defined for this event. The decision about an early termination will be made by the principle investigator.

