For this purpose 3 parallel groups of 20 healthy men will be formed. One group will be treated with ezetimibe (10 mg/day), one with 40 mg/day of simvastatin and another with ezetimibe (10 mg/day) plus simvastatin (40 mg/day). Each treatment period will last for 2 weeks. Blood drawing will be performed at baseline (before the initiation of treatment) and at the end of the 2 weeks. (storing of the samples at  $-80^{\circ}$ ). The measurements involved in this study include the determination of the lipoprotein concentrations in serum, isolation of the mononuclear cells, measurement of LDL receptor mRNA from the peripheral blood mononuclear cells, measurement of HMG-CoA reductase mRNA levels in peripheral blood mononuclear cells, measurement of the LDL-receptor protein concentrations on the surface of peripheral blood mononuclear cells. Furthermore, the serum lathosterol to cholesterol concentrations will be measured as a surrogate marker of the HMG-CoA reductase activity.

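### The per-arm quota of completers, with drop-outs replaced, has no concealed rule for allocating replacements and invites a completers-only comparison

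*Protocol*

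**What the plan says.** Appendix 4, Number of centers and number of subjects, defines the sample by completion and by arm: "20 completed cases per group, drop-outs will be replaced", followed by "Total number: 60 completed subjects". Section B.10 (Interim analysis and criteria for early termination) adds: "The planned number of participants and the analyses will have to be reached before the study will be evaluated".

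The only allocation method is in Appendix 4, Randomization: "Randomization will be performed according to a predetermined random list (balanced 6-block design) by use of sealed envelopes". That section states that all enrolled men are randomised, but it does not mention replacements. Under Study medication the protocol says "There will be open label treatment", and the trial has one centre.

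Under Study Schedule, men are randomised at Visit 1. The baseline study sample and the tablets follow at Visit 2, up to a week later. Visit 3, 14 days after that, gives the only on-treatment sample for the study parameters. No sample is scheduled for a man who stops early.

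Section A.10 (Multicenter trials) gives the recruitment figure: "Approximately 60 subjects will be recruited at the University of Cologne".

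**The concern.** A quota of completers in each arm sits badly with a concealed list. Once someone has dropped out, the number still missing from each arm is known. With open-label treatment at one site, the people enrolling the next man also know which arm is short. If that man is recruited to fill the gap, his treatment is settled before he is approached, and the sealed envelope protects nothing. Selection of late entrants can then depend on the arm they will join.

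A second problem lies in who is counted. Completion happens after randomisation, and it may depend on treatment: tolerability may differ, and one arm takes two tablets a day against one in the others. A man may also leave after learning his arm at Visit 1 and before taking any tablet. Replacing him with another completer restores the count but not the randomised comparison.

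**Working it through.** **Inputs from the protocol.** Three arms, 20 completers each, 60 in total; list balanced in sixes; open label; one centre. The protocol states no alpha, power, effect size, standard deviation (SD) or drop-out rate, so the 20 per arm cannot be re-derived, and every drop-out rate below is an assumption.

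**1. The plan's own figure.** 3 × 20 = 60. I read the block design as blocks of six men, two per arm, because six blocks of ten could not be balanced over three arms. Then 60 / 6 = 10 blocks and 10 × 2 = 20 per arm. The figures agree, provided nobody drops out.

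**2. Chance that nobody drops out among 60, (1 − d)^60.**
- d = 5%: 0.95^60 = 4.6%
- d = 10%: 0.90^60 = 0.2%

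**3. Number randomised to obtain 60 completers, 60 / (1 − d), rounded up.**
- d = 5%: 63.2, so 64
- d = 10%: 66.7, so 67
- d = 15%: 70.6, so 71

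**4. What happens if each replacement takes the next envelope.** This was simulated by continuing the blocks of six, with drop-out independent of arm and 20,000 runs per rate.

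| Assumed drop-out | First 60 completers split exactly 20/20/20 | If recruitment continues until every arm has at least 20: mean randomised | Mean completers | More than 60 completers |
|---|---|---|---|---|
| 5% | 22% | 65.3 | 62.0 | 78% |
| 10% | 12% | 70.0 | 63.0 | 88% |
| 15% | 8.5% | 75.1 | 63.8 | 92% |

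Keeping to the list therefore usually misses either the exact 20 per arm or the total of 60. Meeting both exactly would usually require steering a late entrant to the short arm.

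**5. Size of a completer effect (illustration).** Suppose a share p of one arm leaves and their mean change differs from that of the completers by D. The completer mean is then off by p × D. With p = 0.10 and D = 1 SD, this is 0.10 SD. The standard error of a two-arm difference at 20 per arm is √(2/20) = 0.316 SD, so the shift is 0.10 / 0.316 = 0.32, about one third of a standard error.

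**6. Cost of relaxing the quota.**
- 18 per arm instead of 20: √(20/18) = 1.054, a standard error about 5% wider.
- An uneven pair of 18 and 22: √(1/18 + 1/22) = 0.318 against 0.316, about 0.5% wider.

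**The case against.** Three stronger readings are tempting, and the document does not support them.

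- **A reader might infer that the text forces replacements into a known arm.** It does not. It says only that drop-outs are replaced. The Randomization section covers all enrolled men, which on its face includes replacements, and 20 could be read as a minimum with the list simply continued. That route stays concealed, at the price of more than 60 completers in most cases.
- **A reader might infer that the analysis is restricted to completers.** The quota governs recruitment. No analysis population is named, and a statistical analysis plan that is not shown may define one. Section B.10 rules out early evaluation and does not mention completers.
- **A reader might see a contradiction between Section A.10 and Appendix 4.** A.10 gives an approximate figure for men recruited, and 64 recruited for 60 completed would fit it.

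The context also counts against a heavy charge. This is a 14-day pharmacodynamic pilot in healthy men, and wanting subjects who actually took the drug is a reasonable aim. Drop-out may be low, and the rates and the 1 SD difference used above are mine.

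These objections limit the claim but do not remove it. The quota is stated per arm and in total, evaluation is tied to reaching the planned number, and no rule prevents directed replacement. Allocation of replacements is trial conduct: a later analysis plan cannot restore concealment or supply samples that were never taken.

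**Conclusion.** The point holds in a limited form. The protocol fixes a completer quota per arm and leaves the allocation of replacements open, in a setting where the short arm is known to those enrolling. If 20 and 60 are held exactly, concealment would usually be lost for some late entrants. Under next-envelope replacement, the exact split arises in only about 22% of cases at 5% drop-out and 8.5% at 15%. A completers-only comparison is invited by the rule and by the lack of a scheduled sample for men who stop, but it is not prescribed.

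The likely size is modest. In the illustration, the shift is about a third of a standard error, and with few drop-outs it would be less. This rests on assumed drop-out of 5–15%, on drop-out independent of arm in the simulation, and on an assumed 1 SD difference between leavers and completers. The case for change is that the better rule costs almost nothing.

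**What to change.** In Appendix 4, Number of centers and number of subjects:

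- State that any additional man takes the next sealed envelope in sequence and is never assigned in order to fill an arm.
- Call 20 completers per arm an approximate target, and word the condition in Section B.10 to match.

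In Appendix 4, Study Schedule: ask men who stop study tablets to attend Visit 3 for the fasting sample.

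For the analysis: include all randomised men with baseline and Visit 3 data in their allocated arm, give the completer analysis alongside, and report drop-outs by arm with reasons. Men lost before Visit 2, or without a Visit 3 sample, still cannot contribute a change from baseline, so the report by arm is needed to show how many they are.

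Cost: changes of wording and a few extra Visit 3 attendances. Arms may end slightly unequal or slightly below 20 completers, for which the calculation above gives a loss of precision of about 5% at 18 per arm.
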